### Main study parameter/endpoint

Pathological response rate (percentage necrosis in comparison to tumour cells in the resected specimen) after CRT, determined by an expert pathologist according to the Mandard Tumour Regression Grade (TRG).

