### Other study parameters

Patient characteristics: age, sex, length, weight, cTNM, WHO performance status, extramural vascular invasion, mesorectal fascia involvement, lateral lymph node involvement.

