### Statistical analysis

All main analyses will be performed according to the intention to treat principle using appropriate statistical software, such as R Project for Statistical Computing version 4.0.4. (https://www.r-project.org/) and SPSS version 21.0 (SPSS inc., Chicago, IL). ctDNA methylation levels will be scored high/low relative to the median value in the cohort. Missing samples will not be replaced, because a dropout rate taken into account in the sample size calculation.

We will perform adaptive group-regularized logistic ridge regression followed by post hoc group-weighted elastic net feature selection as described before [10]. In this innovative method group-regularisation of all markers is based on auxiliary data that is provided separately to the model resulting in improved marker selection. In our case this auxiliary data will consist of tissue-based comparison measures like fold changes in DNA methylation and RNA expression between patients with and without a pathological response. When sufficiently promising a targeted assay can be developed for the most optimal marker panel to reduce costs and facilitate clinical implementation.

Obtained data from patients following a watch and wait approach due to a sustained clinical response will be analysed as a separate subgroup since in these patients no pathological response can be determined. These patients will also follow the regular follow-up and will be analysed conform the other patients, only as a subgroup.

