### Secondary study parameter(s)

In an exploratory analysis we will investigate whether the obtained methylation profiles are associated with our secondary outcome measures Recurrence Free Survival (RFS) and Overall Survival (OS). For this purpose we will perform univariate Cox regression analyses with the resulting methylation summary score for the entire profile as well as the selected marker panel (both continuous and dichotomized on the median). In case of significance (p < 0.1) for the univariate analysis subsequently a multivariate model will be built using known risk factors, including clinical (TNM stage, tumour location, age, gender), and pathological (differentiation grade, microsatellite instability status, TRG) parameters.

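### The only multivariable RFS/OS model specified adjusts the methylation score for TRG, the later outcome the panel is selected to predict, so its hazard ratio leaves out whatever runs through response

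*Protocol article*

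**What the plan says.** The section Secondary study parameter(s) of the protocol article describes an exploratory analysis of the methylation profiles against RFS and OS, in two steps.

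- Step 1: "we will perform univariate Cox regression analyses with the resulting methylation summary score for the entire profile as well as the selected marker panel", each taken as continuous and as split at the median. TRG is not in these models.
- Step 2: "In case of significance (p < 0.1) for the univariate analysis subsequently a multivariate model will be built using known risk factors". The clinical factors named are TNM stage, tumour location, age and gender; the list then continues "and pathological (differentiation grade, microsatellite instability status, TRG) parameters".

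Three other sections bear on this:

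- Main study parameter/endpoint makes Mandard TRG in the resected specimen the main endpoint.
- Study procedures limits MeD-seq profiling of plasma to the baseline sample and the one taken after 1 week of treatment. Primary study parameter(s) says the panel is chosen to predict pathological response.
- Statistical analysis sets watch-and-wait patients apart because "in these patients no pathological response can be determined". It adds that they have regular follow-up and are otherwise analysed like the rest, as a subgroup.

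**The concern.** TRG is treated as one more known risk factor, but it differs in kind from the other covariates named. Those can in principle be known before treatment. TRG is known only after chemoradiation and surgery, later than either blood sample that is profiled, and it is the outcome on which the panel is trained. If methylation bears on recurrence partly because it bears on response, TRG lies on that path, and holding it fixed takes that part away.

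What is at stake is how the adjusted HR is read. Step 2 is the only adjusted RFS/OS estimate that the article specifies. A reader who sees an adjusted HR near 1 may conclude that the score adds nothing to stage and other baseline factors, when it may be doing what the study hypothesises. The model also cannot take in patients without a resection specimen. They are managed without surgery because they responded well, so the loss is selective. Finally, the p < 0.1 condition means that an adjusted HR appears only after a favourable univariate result.

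**Working it through.** **1. The plan's own figures.** The article gives no event count, HR or follow-up time for RFS/OS, so there is nothing to reproduce for this model. Its one calculation, the sample size, supplies usable response rates. With 25% v 62.5% (a 2.5-fold ratio), two-sided alpha 0.05, power 0.8 (the stated beta of 0.8 read as power) and continuity correction, the result is 32 per group, 64 in total, as stated. Then 64 / 0.85 = 75.3, rounded up to 76, against the stated 75. The two rates are an assumption, because the article gives only the ratio.

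**2. Order of events.** Baseline sample, 1-week sample, end of chemoradiation, resection with TRG, then follow-up for recurrence and death. Both profiled samples precede TRG.

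**3. Calculation by hand.** Assumptions: response in 62.5% of low-methylation and 25% of high-methylation patients; non-responders have 3 times the hazard of responders; the score has a direct HR of θ within each response group; h is the hazard of a low-methylation responder. At the start of follow-up:

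- High group: θh × (0.25 × 1 + 0.75 × 3) = 2.5θh
- Low group: h × (0.625 × 1 + 0.375 × 3) = 1.75h
- HR without TRG: 2.5θ / 1.75 = 1.43θ
- HR with TRG held fixed: θ

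Adjustment thus strips out a factor of about 1.43 at the outset, whatever θ is.

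**4. Simulated Cox fits.** Same assumptions, h = 0.1 per year, 5 years of follow-up, n = 60,000:

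| Direct HR (θ) | HR without TRG | HR with TRG | Share of log HR kept |
|---|---|---|---|
| 1.0 | 1.47 | 1.00 | about 0% |
| 1.5 | 2.14 | 1.51 | ln 1.51 / ln 2.14 = 0.412 / 0.761 = 54% |
| 2.0 | 2.68 | 1.98 | ln 1.98 / ln 2.68 = 0.683 / 0.986 = 69% |

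So 100%, 46% or 31% of the log HR is removed. The result does not hinge on the factor of 3. With responder HRs of 0.2, 0.3 and 0.5, a base hazard of 0.15 per year and 3 years of follow-up, the no-direct-effect HRs are 1.66, 1.46 and 1.29 without TRG and 1.00, 0.99 and 1.00 with it. With a direct HR of 1.5 to 2, 46% to 75% of the log HR is kept.

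**5. At the planned size.** With n = 64, h = 0.06 per year and 5 years of follow-up, the expected event share with no direct effect is 0.4375 × (1 − e^−0.3) + 0.5625 × (1 − e^−0.9) = 0.447, or about 29 events. The chance of p < 0.05 for the score, without and then with TRG, is 16% and 4% (direct HR 1.0), 57% and 18% (1.5), and 86% and 47% (2.0). The two models test different hypotheses. The comparison shows only how easily the adjusted result could be taken as negative.

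**6. Watch-and-wait patients.** Their share is not stated. If 10%, 20% or 30% of 75 have no TRG, 67.5, 60 or 52.5 remain for a TRG-adjusted model. With 15% dropout as well, 75 × 0.85 × 0.9, 0.8 or 0.7 leaves about 57, 51 or 45. A model containing TRG cannot be fitted in the watch-and-wait subgroup at all, so these patients cannot be analysed there in the same way as the others.

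**The case against.** The strongest reply is that the question asked, whether the profiles are associated with RFS and OS, is answered by the univariate Cox models, which contain no TRG. That stands. A reader might infer that the plan destroys the effect it looks for. It does not: the unadjusted association is estimated whatever follows, and the adjusted effect vanishes only if the score acts solely through response. The article nowhere claims that. Its Discussion links ctDNA detection to recurrence directly, and its Background describes the effect of chemoradiation on distant metastases and survival as small at most.

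A model with TRG also answers a legitimate question: does the score add to what is known once response is known? That stands too, but the article does not give this as the aim and offers no adjusted model for the other question.

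Four further readings go beyond the text or are not settled by it:

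- **Watch-and-wait patients are lost.** They are lost to this model, not to the study. Analysing them separately is a declared choice, and deleting TRG alone would not pool them with the others.
- **Important baseline factors are left out.** The article collects "extramural vascular invasion, mesorectal fascia involvement, lateral lymph node involvement", and the RFS/OS list does not name them, but that list is introduced as examples and is open. Other study parameters, in the statistical part, also plans regression with known clinical risk factors and says RFS and OS will be measured, though it specifies no RFS/OS model.
- **The model has too many parameters for its events.** That rests on event counts the article does not give, and coding detail may sit in the full plan.
- **The score might come from a later sample.** For a post-surgery sample, TRG would come first. But the article mentions the later samples for RFS/OS only as possible future use and profiles only the two early ones.

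**Conclusion.** The point holds in a limited form. As written, the only multivariable RFS/OS model specified conditions an early score on the later outcome that the panel is selected to predict. Its HR excludes the part of the association that runs through response: all of it under full mediation, and roughly a third to a half of the log HR in the main illustration with a direct HR of 1.5 to 2. Those sizes rest on assumed response rates, hazards and follow-up. That the adjusted HR is not the total prognostic effect of the score whenever response carries part of it does not depend on them. Watch-and-wait patients cannot enter the model, and their absence is selective. The severity is modest: the analysis is exploratory, the primary analysis is untouched, and the unadjusted association survives. What the plan lacks is an adjusted estimate that could be used before TRG is known.

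**What to change.** - Make the main multivariable RFS/OS model the methylation score plus pre-treatment factors only, without TRG. State that TNM means the clinical stage before treatment.
- Fit and report it whatever the univariate p-value.
- Make it applicable to watch-and-wait patients, with a time origin they share with resected patients, such as the date of the blood sample used. Say whether they are pooled or fitted as their own subgroup.
- If TRG is of interest, report a second model in resected patients only, with time counted from surgery, labelled as asking whether the score adds to TRG.

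The cost is a change of wording and one extra model to report. No new data or patients are needed.

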### Other study parameters

In an exploratory analysis we will investigate the methylation profile and treatment response with known clinical risk factors and patient characteristics. Multivariate regression analysis will be performed and also RFS and OS will be measured. Significance is determined to be (p < 0.05). Demographics and baseline characteristics will be summarized descriptively. Descriptive statistics will include median and interquartile range or mean and standard deviation for continuous variables, and frequency counts with percentages for categorical variables. Demographics and baseline characteristics will be summarized.

### Handling and storage of data and documents

After a patient has signed the informed consent form, the patient will be registered by the study coordinator. The study coordinator will give each patient a unique subject number (i.e. not related to patients initials, date of birth or other identifiers), starting from MeD-001. The key to the patient subject number is safeguarded by the local investigator. The registration form will at least include the patients’ subject number, the name of the treating physician and investigator, a statement the patient meets all selection criteria and the date of written informed consent. All patient samples will be coded with the patients’ subject number and unique lab code. The original signed informed consent form will be kept on site in the Investigators Site File. The registration form and the collected patient data will be recorded in a digital database.

Research data will be stored in a Castor database and will be handled confidentially. Research data that can be traced to individual persons can only be viewed by authorized personnel. These persons are the members of the research team, members of the health care inspection, and members of the Medical Research Ethics Committee of the participating hospital. Data review may be necessary in order to ensure the reliability and quality of the research. The handling of personal data is in compliance with the Dutch Data Protection Act (in Dutch: Uitvoeringswet ‘Algemene Verordening Gegevensbescherming).

Collected data, essential documents, source documents and human materials (i.e. blood samples) will be stored for at least 15 years in such a manner that they are protected from accidental loss and can easily be retrieved for review. Essential documents are those documents that permit evaluation of the conduct of a trial and the quality of the data produced. The essential documents may be subject to, and should be available for, audit by the Sponsor’s auditor and inspection by the regulatory authority(ies).

## Discussion

To data no clinical or image-based features were found that predict response to CRT. Tissue-based analyses have been performed to find predictive molecular biomarkers for response to CRT, but to date none of the identified potential markers has been clinically implemented [11]. Gene expression panels were identified that allow for the discrimination between responders and non-responders [12, 13]. However, the need for fresh frozen pre-treatment tissue biopsies with sufficient tumour material hampers validation and subsequent clinical implementation of this type of predictive marker. Next to distinct gene expression profiles, high global DNA methylation levels in pre-treatment biopsies were associated with a poor response to CRT [14]. A biological rationale for this observation was provided by Thienpont et al., who showed that tumour-specific DNA methylation increases under hypoxia, which represents one of the major driving mechanisms behind radiotherapy resistance [8]. In contrast to RNA expression, DNA methylation provides a stable and robust biomarker, which facilitates subsequent validation and clinical implementation. Blood is known to contain circulating cfDNA from dying cells in the body, including ctDNA, rendering so-called liquid biopsies (i.e. blood sampling) a patient-friendly alternative to the traditional tissue biopsy. In addition, liquid biopsies are believed to more accurately reflect potential intra-tumour heterogeneity compared to a single tissue biopsy. The challenge is to distinguish ctDNA fragments from the total pool of cfDNA present in the blood. To date this is predominantly done using tumour-specific DNA mutations, limiting its application to patients carrying a known mutation in the tumour. Notwithstanding this limitation recent studies have shown that detection of ctDNA in the blood is predictive for disease recurrence [15], suggesting liquid biopsies could play a key role in the clinical management of rectal cancer patients. Data on the use of liquid biopsies to determine a tumour’s radio-sensitivity upfront is limited [16], but preliminary work suggests that high ctDNA levels before treatment start are associated with subsequent unresponsiveness of rectal cancer to chemo-radiation therapy. In addition, a spike in the ctDNA level directly after treatment start could reflect response to cytotoxic therapies such as radiotherapy [17]. Recent work by others and us demonstrates that tumour-derived DNA methylation profiles are also detectable in a patient’s blood [7], which is of particular interest for the current proposal considering the above mentioned link between increased DNA methylation levels and radiotherapy resistance. An additional advantage of DNA methylation over currently widely used mutations is the high prevalence of altered DNA methylation markers compared to mutations. Symonds et al. showed that ctDNA could be detected in 70% of pre-treatment blood samples from rectal cancer patients using only 2 methylation markers [18]. In conclusion, we hypothesize that DNA methylation patterns in liquid biopsies may provide a promising and patient-friendly strategy to predict CRT resistance upfront.

## Data Availability

Research data will be stored in a Castor database and will be handled confidentially. Research data that can be traced to individual persons can only be viewed by authorized personnel. Information about pathology material will be stored in databases from IKNL, CBS and PALGA and can be used for further information in the future.

## Abbreviations

CBS: Central Statistical Office
in Dutch: Centraal Bureau voor Statistiek
cfDNA: Cell-free DNA
CRT: Chemoradiation therapy
ctDNA: Circulating tumour DNA
IKNL: Netherlands Comprehensive Cancer Organisation; in Dutch: Integraal Kankercentrum Nederland
FFPE: Formalin-fixed paraffin-embedded
LARC: Locally advanced rectal cancer
METC: Medical research ethics committee (MREC); in Dutch: Medisch-Ethische Toetsings Commissie (METC)
OS: Overall survival
PALGA: Pathological Anatomy National Automated Archive; in Dutch: Pathologisch Anatomisch Landelijk Geautomatiseerd Archief
RFS: Recurrence Free Survival
TME: Total Mesorectal Excision
TNM: The TNM Classification of Malignant Tumors
TRG: Tumour Regression Grade
